## Abstract

**Background:**

In critically ill patients requiring extracorporeal membrane oxygenation (ECMO) therapy, early initiation of continuous renal replacement therapy (CRRT) and beta-blockade of catecholamine-induced inotropic effects may improve outcomes.

**Methods:**

A 2 × 2 partial factorial randomized controlled trial in eligible ECMO patients without a clear indication or contraindication to either intervention is centrally randomly assigned to (A) early or conventional-indicated CRRT and/or (B) beta-blocker or usual care. The primary outcome is all-cause mortality at 30 days for both arms. A total of 496 participants provides 80% power to determine a 20% risk reduction in mortality at 30 days with 5% type I error.

**Discussion:**

This trial will help define the role of early CRRT and beta-blockade in ECMO patients. There have been 89 patients enrolled at 10 hospitals in study A and is ongoing. However, study B was stopped in August 2019 in the absence of any patients being enrolled.

**Trial registration:**

ClinicalTrials.govNCT03549923. Registered on 8 June 2018. World Health Organization International Clinical Trials Registry Platform (WHO ICTEP) network. The Ethics Committee of Beijing Anzhen Hospital Approval ID is 2018013.

## Background

### Introduction

Veno-arterial extracorporeal membrane oxygenation (VA-ECMO) provides short-term circulatory support for critically ill patients with severe cardiac shock, but mortality remains high (60 to 75%) [1] and acute kidney injury (AKI) and fluid overload (FO) are frequent complications [2, 3] that are managed with continuous renal replacement therapy (CRRT) [3–6]. However, the optimal timing of CRRT is uncertain: the positive results of the early vs late initiation of renal replacement therapy in critically ill patients with acute kidney injury (the ELAIN) trial [7] were not confirmed in another study, the Artificial Kidney Initiation in Kidney Injury (AKIKI) [8]. As critically ill patients have excessive sympathetic activation and autonomic dysfunction from high circulating catecholamines that may compromise cardiac function [9–14], beta-blockade could improve outcomes by improving myocardial oxygen consumption, ventricular remodeling, and left ventricular function [15, 16]. A randomized, open, single-center study in patients with septic shock requiring norepinephrine to maintain mean arterial pressure showed a benefit of esmolol on 28-day mortality [17]. The circulatory support offered by ECMO may avoid the negative inotropic effect of beta-blockers in the setting of cardiogenic shock [18]. We designed the EvaLuation of early CRRT and beta-blocker InTervention in patients with ECMO (ELITE) trial to determine the effects of early CRRT versus conventionally indicated CRRT and/or beta-blockade on top of routine care.

### Objective

The objective is to determine whether (A) early CRRT compared to conventional-indicated CRRT and (B) beta-blockade with esmolol compared to standard treatment will reduce 30-day mortality in ECMO patients.

## Methods

### Study design (Fig. 1)

ELITE is a prospective, multi-center, open-label, randomized controlled trial, with a 2 × 2 partial factorial design to evaluate whether early CRRT support and beta-blockade will reduce 30-day mortality in a broad range of ECMO patients admitted to hospitals in China from July 2018. In arm A, patients are randomized to early CRRT within 24 h of initiation of ECMO or to control, regardless of whether there is a conventional indication, or to the control where patients only receive CRRT according to a conventional indication. In arm B, patients are randomized to the intravenous esmolol group or usual care. The trial design and protocol adhere to the Recommendations for Interventional Trials (SPIRIT) criteria [19] (Table 1) and checklist in Table 5 in Appendix. The study is planned to enroll patients from 10 centers in China (see Table 5 in Appendix for the hospital list).

**Fig. 1 Fig1:**
[figure not shown]
Study design. CKD, chronic kidney disease; CRRT, continuous renal replacement therapy; ECMO, extracorporeal membrane oxygenation; ICU, intensive care unit; VA-ECMO, veno-arterial extracorporeal membrane oxygenation

**Table 1 Tab1:** Study period

	CRRT screening	CRRT randomization	Beta-blocker screening	Beta-blocker randomization	Days post-randomization			
					Day 3	Day 7	Day 30	Day 365
Window for time for evaluation							± 5 days	± 35 days
Visit number		1		1	2	3	4	5
Informed consent		×		×				
Demographic data	×		×					
Physical measures	×	×	×	×				
Medical history		×		×				
Concomitant medications	×	×	×	×	×	×	×	×
Physical examinations^a^		×		×				
Vital signs^b^		×		×	×	×		
Complete blood count^c^		×		×	×	×		
Arterial blood gas^d^		×		×	×	×		
Biochemistry items^e^	×		×		×	×		
Coagulation indexes^f^		×		×	×	×		
UCG^g^		×		×	×	×		
Intake and output volume in 24 h					×			
Medication, type, and dose^h^		×		×	×	×	×	×
Mechanical ventilation and mode		×		×	×	×	×	
Left ventricular unloading method					×	×	×	
RRT	×				×	×	×	×
APACHE II score		×		×				
SOFA score		×		×				
EQ-5D score								×
SAEs					×	×	×:	×

^a^Physical examinations: height (cm) and weight (kg)

^b^Vital signs: blood pressure (mmHg), pulse (beats/min), heart rate (beats/min), temperature (°C), and respiratory (/min)

^c^Complete blood count: white blood cell count (10^3^/mm^3^), hemoglobin (g/dL), and platelet count (10^9^/L)

^d^Arterial blood gas: PH, PaO_2_ (mmHg), PaCO_2_ (mmHg), K^+^ (mmol/L), Na^+^ (mmol/L), hematocrit (%), and lactic acid (mmol/L)

^e^Biochemistry items: creatine (μmol/L) and total bilirubin (μmol/L)

^f^Coagulation indexes: PT (s) and APTT (s)

^g^UCG: left ventricular ejection fraction (%), left ventricular end-diastolic diameter (cm), moderate and above pulmonary hypertension, and moderate and above tricuspid regurgitation

^h^Medication: dopamine, dobutamine, epinephrine, norepinephrine, vasopressin, pituitrin, milrinone, and beta blockers

### Eligibility

The broad inclusion criteria are used for both arms, whereby adult patients who have received ECMO for any reason within 24 h and 7 days, for arms A and arm B, respectively, are eligible (Tables 2 and 3). Patients are excluded from arms A and B if they had a definite indication or contraindication to either CRRT or beta-blockers, respectively. As ECMO is often initiated by a specialist team to rescue and transfer patients to larger hospitals in China, a timeframe of 24 h after ECMO implantation was used for early CRRT in arm A, while a relatively stable hemodynamic status (dopamine/dobutamine < 5 μg/kg/min, with no administration of adrenaline or norepinephrine) and within 7 days after initiation of ECMO was required for eligibility into arm B. Identification of potentially eligible patients is the responsibility of the ECMO team in participating centers. After ECMO implantation or when the patient is transferred to the participating center, eligibility for study arm A will be assessed. Prior to 7 days after ECMO implantation, when patients are stable on ECMO, eligibility for study arm B will be assessed.

**Table 2 Tab2:** Inclusion and exclusion criteria for study A

Inclusion criteria	
Patients receiving VA-ECMO for any reason within 24 h	
Provision of informed consent	
Exclusion criteria	
Age < 18 years	
Receiving ECMO bridging to heart transplantation	
With convention indication of CRRT: AKI prior to enrollment caused by any reason, at least one of the following criteria is met:	
Severe hyperkalemia (> 6.5 mmol/L)	
Metabolic acidosis (pH < 7.2)	
Pulmonary edema	
Blood urea nitrogen level > 112 mg/dL	
Oliguria (urine output < 200 mL/12 h) for more than 72 h	
CKD, with estimated GFR<30 mL/min	
Have already initiated CRRT	
Active hemorrhage/thrombotic thrombocytopenic purpura	
Receiving ECMO again during hospitalization or respiratory failure has already initiated VV-ECMO or extracorporeal carbon dioxide removal device before the initiation of VA-ECMO of this time	

*AKI* chronic kidney disease, *CKD* chronic kidney disease, *CRRT* continuous renal replacement therapy, *ECMO* extracorporeal membrane oxygenation, *GFR* glomerular filtration rate, *VA-ECMO* veno-arterial extracorporeal membrane oxygenation, *VV-ECMO* veno-venous extracorporeal membrane oxygenation

**Table 3 Tab3:** Inclusion and exclusion criteria for study B

Inclusion criteria	
Patients receiving VA-ECMO for any reason	
Dopamine/dobutamine < 5 μg/kg/min, no administration of adrenaline or norepinephrine	
Within 7 days after initiation of VA-ECMO	
Exclusion criteria	
Age < 18 years	
Receiving ECMO bridging to heart transplantation	
Contraindications or intolerance to beta-blockers	
Moderate or severe bronchial asthma attack or history of bronchial asthma	
Sinus bradycardia (heart rate < 60 bpm)	
Type II second-degree or third-degree AVB	
Allergy to esmolol	
Receiving ECMO again during hospitalization or respiratory failure has already initiated VV-ECMO or extracorporeal carbon dioxide removal device before the initiation of VA-ECMO of this time	
Have been on beta-blocker treatment after initiation of ECMO	
Women at child-bearing age, pregnant or positive pregnancy test	

*ECMO* extracorporeal membrane oxygenation, *AVB* atrioventricular block, *VA-ECMO* veno-arterial extracorporeal membrane oxygenation, *VV-ECMO* veno-venous extracorporeal membrane oxygenation

### Randomization

All eligible patients are centrally randomized in a 1:1 ratio to either early CRRT or conventional indication CRRT, and/or beta-blocker group or usual care (control) groups, via a computer-generated randomization schedule, stratified by age (< 65 vs. ≥ 65 years) and implantation of ECMO for extracorporeal cardiopulmonary resuscitation (yes vs no). The sequence of randomization is generated by an independent statistician, using SAS version 9.4. Investigators use a cellphone application to confirm eligibility and obtain the randomized treatment allocation.

### Interventions

Patients assigned to early CRRT should have it applied concurrently with ECMO treatment and continued for ≥ 12 h. Those assigned to standard therapy should receive CRRT according to the 2012 Kidney Disease: Improving Global Outcomes (KDIGO) Clinical Practice Guideline for AKI stage 3 and have at least one of the following criteria met: severe hyperkalemia (> 6.5 mmol/L), metabolic acidosis (pH < 7.2), pulmonary edema unresponsive to diuretic therapy, requiring oxygen flow rate of > 5L/min to maintain an oxygen saturation (SpO_2_) of > 95% or requiring a forced inspired oxygen concentration (FiO_2_) of > 50% on ventilation, blood urea nitrogen level > 112 mg/dL, or oliguria (urine output < 200 mL per 12 h) for > 72 h. CRRT can be initiated or discontinued according to the attending clinician’s decision in managing the patient.

In arm B, patients assigned to the intervention group are to receive a continuous infusion of esmolol on top of conventional management, commencing at 25 mg/h and increasing by 25 mg/h every 20 min until the heart rate is reduced to 75 ± 5 bpm or an upper dose limit of 2000 mg/h is reached. Esmolol infusion should be continued to maintain the heart rate threshold or according to the clinician’s discretion until discharge from the intensive care unit (ICU) (or death, if sooner). Oral beta-blockers should be introduced before esmolol is withdrawn. Esmolol can be transiently stopped or completely withdrawn should a patient develops third-degree atrial-ventricular block, bradycardia (< 60 bpm), extreme left ventricular systolic dysfunction, aortic valve dysfunction, or severe cardiogenic pulmonary edema. Patients in the control group will not receive any type of beta-blockers, unless the clinician considers there is a strong indication. Concomitant diseases will be treated following the current guidelines.

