### Sample size

Sample size calculation is performed using the software PASS 15.0.5 based on the following assumption: a 70% 30-day mortality in the control group and a 20% relative risk reduction for each intervention (early CRRT and beta-blocker). The estimate of the intervention’s effect size was based on clinical expertise and the clinical significance of an intervention, no loss of follow-up or crossover, and 5% type I error and 20% type II error. We assume no interaction between interventions, as the overlap of the time of interventions would be limited and no carry-on effect expected. A total of 496 patients (248 per group) are required for each arm.

To achieve adequate participant enrolment to reach the target sample size, the study will be conducted at 10 high-volume centers in China. A smartphone application has been developed to facilitate randomization at the emergency room.

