### Monitoring

The data monitoring committee (DMC) consists of a critical care physician, nephrologist, and cardiovascular expert, all experienced in clinical research. The principal investigator will report the process of the trial, quality of data collected, adverse events, and protocol deviation and violation to the DMC. The DMC will meet every 6 months during the conduction of the trial. No interim analysis for efficiency is planned as the assumptions in sample size calculation are less likely to be changed.

An investigator meeting is held annually to communicate the progress, quality control, and approaches to improve recruitment and address any quality of data issues.

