## Discussion

Being one of the most seriously ill groups in clinical practice, with high mortality and requiring heavy use of critical care resources, there are considerable challenges to generate reliable evidence to guide the management of ECMO patients. Our ELITE trial attempts to address two important clinical questions with strong pathophysiological mechanisms.

A multicenter retrospective cohort study has shown that FO is common in a pediatric population (peak FO ≥ 10% in 84.8%, ≥ 20% in 67.2%, and ≥ 50% in 29%) [20] where FO has consistently been shown to be associated with adverse outcomes [21–23], while a meta-analysis of observational studies has shown lower mortality in those who receive CRRT [24]. These data suggest that early initiation of CRRT to avoid FO in the context of ECMO may be beneficial. The Kidney Interventions During Membrane Oxygenation (KIDMO) study showed that CRRT use was 43%, 16%, and 35% of patients for FO, for FO prevention, and for AKI, respectively, after ECMO [25]. However, there has not been a randomized trial to support these approaches. So, we designed this ELITE trial. As the closing of arm B, the question of whether beta-blocker is efficient in patients with ECMO remains unaddressed, and more effects should be made.

Other limitations of our trial include the lack of blinding, and for practical reasons, recruitment has been slow due to the small number of patients receiving ECMO despite the expectation of a least 10 cases treated annually across our network of 30 ICUs in China. We did not stratify our randomization by ECMO centers but will perform a subgroup analysis to explore the effect between small and large centers.

In summary, the ELITE trial is the first randomized controlled trial of critically ill patients receiving ECMO support, powered to test the effects of early CRRT versus conventional timing of CRRT on 30-day mortality. The results should inform the management of this important patient group.

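### The clinician-discretion sentence on CRRT names no group, criterion or time limit, so read literally it permits the crossover that the control rule and the sample size exclude

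*Protocol article*

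**What the plan says.** All references are to the Protocol article.

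- **Study design** defines the study A comparator as "the control where patients only receive CRRT according to a conventional indication".
- **Interventions** makes this specific. Controls are to receive CRRT under the KDIGO "Clinical Practice Guideline for AKI stage 3 and have at least one of the following criteria met". The criteria cover hyperkalemia, acidosis, diuretic-resistant pulmonary edema with an oxygen requirement, blood urea nitrogen and prolonged oliguria. The early group is to have CRRT alongside ECMO for at least 12 h.
- The study A paragraph of **Interventions** then closes: "CRRT can be initiated or discontinued according to the attending" clinician's decision.
- The study B control rule in the same section is worded differently. It names the control group and withholds beta-blockers "unless the clinician considers there is a strong indication".
- **Sample size** assumes 70% control mortality at 30 days, a 20% relative reduction, 5% type I and 20% type II error, and "no loss of follow-up or crossover". It arrives at 248 per group.
- **Statistical analysis** is by intention to treat, with two-sided tests.
- **Monitoring** plans no interim efficacy analysis because "the assumptions in sample size calculation are less likely to be changed".

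**The concern.** Study A compares two rules for when CRRT starts, so the control rule is half of the experiment. The discretion sentence directly follows that rule and carries no limit of its own, and nothing elsewhere in the article supplies one. Followed as written, it allows two departures from the intended contrast: a control start without a listed criterion, and an early-group stop before 12 h.

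Intention-to-treat analysis stays valid for the strategies as delivered, but discretionary control starts remain in the control group and shrink the difference. The trial is open-label, so the treating clinician knows the allocation when deciding. A null result could then mean either that early CRRT has no effect or that many controls received CRRT at discretion. Ten centers could also read the sentence differently. Because a permitted start is not a protocol deviation, a report of deviations to the DMC need not include it.

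**Working it through.** **1. The texts side by side**

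| Place | Who | When CRRT may start or stop |
|---|---|---|
| Study design | Control | Only on a conventional indication |
| Interventions, control rule | Control | AKI stage 3 plus at least one listed criterion |
| Interventions, early rule | Early group | Alongside ECMO, at least 12 h |
| Interventions, next sentence | No group named | Start or stop at the clinician's decision |
| Sample size | Both | No crossover |

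The fourth row, taken literally, overrides the second and third and permits what the fifth sets to zero.

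**2. The plan's own sample size**

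Inputs: p1 = 0.70; p2 = 0.70 × 0.80 = 0.56; two-sided 5% (z = 1.960); 1:1 allocation. The mean proportion is 0.63.

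n per group = [1.960 × √(2 × 0.63 × 0.37) + z(power) × √(0.70 × 0.30 + 0.56 × 0.44)]² / 0.14²

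The square roots are 0.6828 and 0.6756.

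- 80% power: (1.3382 + 0.5686)² / 0.0196 = 185.5, so 186 per group (372 in total).
- 90% power: (1.3382 + 0.8658)² / 0.0196 = 247.8, so 248 per group (496 in total).

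The stated 248 therefore does not reproduce at 80% power; it is the 90% figure. As a check, power at 248 is Φ[(0.14 × √248 − 1.3382) / 0.6756] = Φ(1.283) = 90.0%.

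**3. What control crossover does at 248 per group**

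Let c be the share of controls who cross over and k the share of the 14-point benefit they receive. Control mortality becomes 0.70 − 0.14 × c × k, and the early group stays at 0.56. Both c and k are assumptions.

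| c | Control mortality, k = 1 | Power, k = 1 | Control mortality, k = 0.5 | Power, k = 0.5 |
|---|---|---|---|---|
| 0% | 0.700 | 90.0% | 0.700 | 90.0% |
| 10% | 0.686 | 82.7% | 0.693 | 86.7% |
| 20% | 0.672 | 72.9% | 0.686 | 82.7% |
| 30% | 0.658 | 60.9% | 0.679 | 78.1% |

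Power equals 80% at c = 13.0% for k = 1 (0.130 × 248 ≈ 32 controls) and at c = 26.0% for k = 0.5 (0.260 × 248 ≈ 64 controls).

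**4. Sensitivity to the test**

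The planned primary test is the log-rank. Under proportional hazards the hazard ratio is ln(0.44) / ln(0.30) = 0.682, and 496 × 0.63 ≈ 312 deaths are expected. Schoenfeld's approximation gives 92.3% power without crossover, and 85.7%, 76.2% and 64.3% at 10%, 20% and 30% full-benefit crossover. The pattern is the same, two to four points higher.

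**The case against.** **Safety discretion is normal.** The sentence may only mean clinical judgement within the criteria, or after the 12 h period, and no crossover is a planning assumption, not a rule of conduct. This stands in part: calling it a flat contradiction would go too far. But the article does not state the milder reading, and study B's control rule shows that an override can be tied to a group and a reason.

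**Crossover is not invisible.** A reader might infer that control CRRT would go unrecorded. The documents do not support that. Table 1 schedules RRT at days 3, 7, 30 and 365, with blood gases and biochemistry at days 3 and 7, and Data management collects CRRT duration. What is not listed is the reason for starting, which separates a conventional start from a discretionary one. Nor does Monitoring say that CRRT use by group is withheld from the DMC.

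**No rate can be projected.** A reader might take the cited cohort in the Discussion, where "CRRT use was 43%, 16%, and 35% of patients for FO, for FO prevention, and for AKI, respectively", and turn 43% + 16% = 59% into an expected crossover rate. That fails. The documents do not give the share of controls who would receive CRRT. Prevention of fluid overload (16%) is less common there than AKI (35%). Some fluid overload would also qualify through the pulmonary edema criterion. The figures show only that fluid overload is a common reason for CRRT on ECMO.

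**Full benefit is a harsh case.** A control who starts CRRT days later has not received early CRRT, and full benefit would mean that timing is irrelevant. This stands: k = 1 is a bound. With a quarter of the benefit, power is still 84.8% at 30% crossover.

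**Recruitment matters more.** With the 89 patients enrolled so far (44.5 per group), power without crossover is Φ[(0.14 × √44.5 − 1.3382) / 0.6756] = 27%. True, but it does not make the sentence clearer, and a smaller trial has less contrast to spare.

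**Conclusion.** The point holds as a wording fault with consequences. The discretion sentence has no group, criterion or time limit. Read literally, it permits control starts and early-group stops that conflict with the control rule, the 12 h minimum and the no-crossover assumption. It is worth correcting but does not invalidate the trial.

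Its size can be given only as a tolerance. At the planned inputs, 248 per group keeps at least 80% power up to about 13% control crossover with full benefit, or 26% with half. This rests on the 70% and 56% mortality assumptions, a two-proportion approximation and crossover in the control group only.

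Two stronger readings are not supported. The first is that the trial is underpowered because of crossover: the documents give no rate, and 248 per group starts from 90%. The second is that this surplus was meant as room for crossover: Sample size labels 496 as 80% power and explicitly assumes none.

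**What to change.** **Interventions.** Replace the discretion sentence with one rule per group.

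- *Control:* CRRT only when a listed criterion is met, or for a documented urgent safety reason. A start of the second kind is recorded and counted as crossover. Copying study B's clause alone would restrict little, since it too rests on clinician judgement; the documented reason does the work.
- *Early group:* stopping at discretion only after 12 h, or earlier for a documented safety reason.

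**Monitoring.** Report control starts outside the criteria to the DMC at its 6-monthly meetings.

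**Sample size.** State that 248 per group gives 90% power at 70% versus 56%, two-sided 5%, with no crossover, and that 80% would need 186. Add as a sensitivity statement that power falls below 80% above about 13% control crossover with full benefit, or 26% with half. Do not present this as a planned allowance, and do not claim an expected rate.

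**Cost.** A short amendment and one more recorded item, the reason for starting CRRT. Some discretionary starts become reported crossovers. The target of 496, the entry window and the primary analysis do not change, the 89 enrolled patients stay in, and clinicians keep a safety override.
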